## Abstract

**Background:**

Burnout is an occupational syndrome that leads to mental health problems, job turnover, and patient safety events. Those caring for critically ill patients are especially susceptible due to high patient mortality, long hours, and regular encounters with trauma and ethical issues. Interventions to prevent burnout in this population are needed. Preliminary studies suggest debriefing sessions may reduce burnout. This study aims to assess whether participation in regular debriefing can prevent burnout in intensive care unit (ICU) clinicians.

**Methods:**

A randomized controlled trial will be conducted in two large academic medical centers. Two hundred ICU clinicians will be recruited with target enrollment of 100 physicians and 100 non-physicians (nurses, pharmacists, therapists). Participants must have worked in the ICU for the equivalent of at least 1 full time work week in the preceding 4 weeks. Enrolled subjects will be randomized to virtually attend biweekly debriefing sessions facilitated by a psychotherapist for 3 months or to a control arm without sessions. Our debriefs are modeled after Death Cafés, which are informal discussions focusing on death, dying, loss, grief, and illness. These sessions allow for reflection on distressing events and offer community and collaboration among hospital employees outside of work.

The primary outcome is clinician burnout as measured by the Maslach Burnout Inventory (MBI) Score. Secondary outcomes include depression and anxiety, as measured by the Patient Health Questionnaire 8 (PHQ-8) and Generalized Anxiety Disorder 7-item scale (GAD-7), respectively. Questionnaires will be administered prior to the intervention, at 1 month, at 3 months, and at 6 months after enrollment. These values will be compared between groups temporally. Qualitative feedback will also be collected and analyzed.

**Discussion:**

With ICU clinician burnout rates exceeding 50%, Death Café debriefing sessions may prove to be an effective tool to avert this debilitating syndrome. With COVID-19 limiting social interactions and overloading ICUs worldwide, the virtual administration of the Death Café for ICU clinicians provides an innovative strategy to potentially mitigate burnout in this vulnerable population.

**Trial registration:**

ClinicalTrials.gov NCT04347811. Registered on 15 April 2020

## Administrative information

The order of the items has been modified to group similar items (see http://www.equator-network.org/reporting-guidelines/spirit-2013-statement-defining-standard-protocol-items-for-clinical-trials/).

## Introduction

### Background and rationale {6a}

Burnout is an occupational syndrome characterized by emotional exhaustion, distant or indifferent attitude toward work, and reduced sense of personal accomplishment [1]. It affects physicians and ancillary healthcare providers on a national scale [2–7]. The prevalence of burnout is as high as 60% in hospital employees at one of our institutions, an urban, academic, Level One trauma center [7]. Those caring for critically ill patients are especially susceptible to burnout due to features specific to the intensive care unit (ICU) such as high patient morbidity and mortality, long hours, and regular encounters with trauma and ethical issues. These experiences lead to moral distress and compassion fatigue [5, 8–12].

Burnout not only impacts the ability to enjoy work but also may lead to depression, posttraumatic stress disorder, substance abuse disorder, and suicidality [4, 5, 13, 14]. It can increase the rate of job turnover, leading to caregiver shortages [5, 10]. Most significantly, burnout is known to contribute to patient safety events [5, 15]. Physicians and nurses with burnout are more likely to make medical errors, deliver a lower quality of care, and communicate poorly with their patients [4, 14, 16–28]. Burnout is associated with higher 30-day mortality and rates of hospital-acquired infections [5].

In spite of the growing awareness of the consequences of burnout, interventions to prevent or address burnout are sparse in the literature [5, 15, 29]. Most interventions to date have focused on reduction in work hours, development of wellness curricula, and mindfulness promotion [29–32]. Preliminary studies suggest that debriefing opportunities may reduce burnout through enhancement of social support and interprofessional collaboration [33–37].

Death Cafés are a specific form of debriefing which have emerged internationally for the general public using informal discussion on topics of death, dying, loss, and illness to mitigate distress [38, 39]. During the COVID-19 pandemic, many community-based Death Cafés shifted to virtual modalities to respect social distancing guidelines. Healthcare worker specific Death Cafés have been described with similar structure and function to community initiatives with the aim to foster reflection on distressing patient events while developing a sense of community and collaboration among employees [7]. This would be the first study to report on the effects of hospital-based Death Cafés and the first study to report on the efficacy of virtual debriefing sessions for burnout prevention in an ICU setting.

### Objectives {7}

Systematic Trial of PrevenTing Healthcare Employee Burnout Using Reflection & Nourishment (STOPTHEBURN) is a single-center 2-arm randomized controlled trial that will evaluate the impact of Death Café debriefing interventions on burnout in healthcare employees. We hypothesize that participation in Death Cafés will lead to lower rates of burnout in physicians and staff (nurses, pharmacists, therapists).

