## Methods: participants, interventions, and outcomes

### Study setting {9}

Our two study sites are academic hospitals with large medical and surgical ICUs in New Orleans, LA. Notably, one of the hospitals has a wellness taskforce, B-Well, with volunteer staff participation to address professional burnout through supporting employee health and wellbeing. Since 2017, B-Well sponsors quarterly Death Cafés for hospital employees facilitated by authors RH and NR. Participation in the B-Well events is voluntary and not specific to ICU clinicians.

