### Recruitment {15}

Recruitment will be performed in person at each ICU site and electronically via email to employee listservs on a biweekly basis until target enrollment is reached. Recruitment will involve screening for eligibility, providing potential participants with information about the study, and obtaining informed consent. Participants will be offered compensation for completion of a minimum number of study procedures. This will be $140 for completion of the Death Café study arm and $40 for the control arm.

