## Trial status

Trial enrollment will begin July 1, 2020, at UMC and is anticipated to conclude July 1, 2021. The current study protocol is dated May 4, 2020.

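### The Objectives call a two-hospital trial single-center, and neither the stated allocation scheme nor the analysis as described names hospital, although one hospital already offers Death Cafés

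*Protocol article*

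**What the plan says.** On the number of centers, the protocol article says:

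- Objectives {7}: the trial "is a single-center 2-arm randomized controlled trial".
- Abstract, Methods: "A randomized controlled trial will be conducted in two large academic medical centers".
- Study setting {9}: "Our two study sites are academic hospitals with large medical and surgical ICUs in New Orleans, LA".
- Recruitment {15}: "Recruitment will be performed in person at each ICU site".
- Trial status: "Trial enrollment will begin July 1, 2020, at UMC". This says where enrollment starts, not how many sites there are.

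On how the hospitals differ, Study setting {9} reports that one of them has a wellness taskforce: "Since 2017, B-Well sponsors quarterly Death Cafés for hospital employees". The facilitators are the two psychotherapists who also lead the trial sessions. The same section adds: "Participation in the B-Well events is voluntary and not specific to ICU clinicians".

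On allocation, Sequence generation {16a} randomizes physician and non-physician pairs to the same arm. Profession is the only balancing factor, and the sections on concealment and implementation add none.

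On analysis, Statistical methods {20a} names age, gender and presence of an outcome as risk factors, and a mixed model whose terms are not listed. Methods for additional analyses {20b} names role and wellness questions. Challenges, in the Discussion, names demographic, personal-wellness and work-environment factors. None of these mentions hospital.

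**The concern.** One center and two centers cannot both be right, and all of these statements are current text. The contradiction deserves more than a copy-edit because the authors themselves single out a difference between the hospitals that bears on the tested intervention. Staff at one hospital could have attended Death Cafés before the trial and may be able to attend them during it. Hospital may therefore be related both to baseline burnout and to outside exposure.

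The scheme already constrains allocation to balance profession, but not hospital. If by chance one arm draws more of its participants from one hospital, any difference in burnout between the hospitals enters the comparison of arms as extra noise. A model without hospital would also leave that part of the variation in the residual.

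**Working it through.** **1. Number of centers.** Objectives {7}: one. Abstract and Study setting {9}: two. Recruitment {15}: more than one. Trial status names one hospital, but only as the place where enrollment begins, so it supports neither count. The conflict lies between the Objectives and the other three places.

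**2. Inputs for chance imbalance.** From the article: 200 participants, 1:1 allocation (100 per arm), allocation in pairs of one physician and one non-physician. Not given, hence assumed: the hospital split, and whether the two members of a pair come from the same hospital.

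**3. Hospital unrelated to pairing.** With share *s* of participants from one hospital, the standard deviation of the between-arm difference in that share is √[s(1 − s) × 2/100].

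- s = 0.5: √(0.25 × 0.02) = 0.071. A difference of 10 points is 0.10/0.071 = 1.41 SD, with two-sided probability 0.16 by the normal approximation. A direct calculation gives about 0.17, with a 95% range of about ±14 points.
- s = 0.7: SD 0.065, probability 0.12.
- s = 0.8: SD 0.057, probability 0.08.

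**4. Pairs formed within hospital.** Each pair then moves as a unit of two, and the SD is multiplied by √2.

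- s = 0.5: 0.071 × 1.41 = 0.10, probability 0.32 by the normal approximation. Exact enumeration with 50 pairs per hospital and an independent fair draw for each pair gives 0.368, with a 95% range of ±20 points. Part of the gap is discreteness: about 9 percentage points of the 0.368 come from imbalances between 10.0 and 10.5 points, and beyond 10.5 points the figure is 27.6%.
- s = 0.7: 0.28. s = 0.8: 0.21 (normal approximation).

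**5. Effect on the result.** Shift in the arm difference = imbalance in hospital share × burnout difference between hospitals. The article does not give the second factor: its only institutional prevalence (Background {6a}) is for one hospital. For illustration, assume a gap of 10 to 20 percentage points:

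- Imbalance of 10 points: 0.10 × 10 to 20 = 1 to 2 points.
- Imbalance of 20 points, the edge of the 95% range in step 4: 0.20 × 10 to 20 = 2 to 4 points.

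The planned effect is 20 points, if the 20% in Sample size {14} means percentage points.

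**6. Precision.** No standard deviation is stated. The one that makes 100 per arm give power 0.8 for a mean difference of 4 (two-sided alpha 0.05) is 4/[(1.960 + 0.842) × √(2/100)] = 10.1. With equal shares, a hospital difference D in mean score accounts for variance D²/4. Removing it raises power from 0.800 to 0.804 (D = 2), 0.815 (D = 4) or 0.835 (D = 6).

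**7. What separate lists achieve.** Separate lists of within-hospital pairs with an independent draw for each pair reproduce step 4 exactly, so they bring no gain. With permuted blocks of, say, four pairs, 50 pairs make 12 full blocks plus 2 pairs, so each hospital puts 24 to 26 pairs in each arm. The worst case is 26/50 − 24/50 = 4 points.

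**The case against.** The strongest reply is that only a wording slip has been shown. Two-site trials need not stratify by site, this one calls itself a pilot, and randomization is unbiased whatever the hospital mix. Chance imbalance is already reflected in the standard error of an unadjusted comparison. Burnout is measured at enrollment and later scores are compared with it, so baseline differences are partly handled. The existing events are quarterly and voluntary, no attendance figure is given, and the pandemic limited in-person sessions, so hospital is a crude proxy for exposure. All of this stands, and it keeps the point modest. It does not remove the contradiction, nor the fact that the stated allocation scheme passes over a site difference the authors themselves highlight, when using it would cost almost nothing.

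A reader might also infer three stronger things that the article does not support:

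- That the analysis leaves hospital out. The mixed-model terms are not listed, and covariates may be set in a full protocol or analysis plan not shown. One can say only that hospital is not named in the analysis described.
- That allocation ignores hospital because the trial was thought of as single-center. Nothing links the two.
- That Trial status confirms a single site. It does not.

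**Conclusion.** The Objectives contradict the abstract, Study setting and Recruitment on the number of centers; that part is certain and clerical. The substantive part is a cheap improvement rather than a flaw that threatens validity: in a two-hospital trial where one hospital already offers the type of session under test, hospital should be used in allocation and named in the model.

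A difference between arms of more than 10 points in hospital share would occur in about 17% of trials if hospital is unrelated to pairing and about 37% if pairs share a hospital. Both figures assume a 50:50 split, which is the least favorable case; uneven splits give less. The shift in the result scales with an unknown between-hospital difference and is probably small.

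It would be tempting to call this bias, or to say that the control arm is contaminated. Neither follows. The imbalance is chance variation, and actual attendance at the existing events by trial participants is unknown. Any such attendance by controls would be a separate matter that stratifying by hospital would not remove.

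**What to change.** 1. Correct the Objectives to two centers.
2. In Sequence generation {16a}, form pairs within hospital and randomize them from a separate list per hospital in permuted blocks. The blocking is essential, because unblocked separate lists would not improve balance (step 7 of the working). Because the trial is open-label, varying the block size would keep assignments hard to predict.
3. In Statistical methods {20a}, name hospital as a fixed effect in the mixed model.

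The target of 200, the surveys and the visit times do not change. The costs are a slightly longer wait for a partner from the same hospital, two lists instead of one, and recording hospital for each participant, which the article does not say is done. If allocation has already started, the first and third changes can still be made, the third before the data are analyzed.

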### Trial design {8}

STOPTHEBURN is a parallel group randomized controlled trial with a 1:1 allocation ratio.

## Methods: participants, interventions, and outcomes

### Study setting {9}

Our two study sites are academic hospitals with large medical and surgical ICUs in New Orleans, LA. Notably, one of the hospitals has a wellness taskforce, B-Well, with volunteer staff participation to address professional burnout through supporting employee health and wellbeing. Since 2017, B-Well sponsors quarterly Death Cafés for hospital employees facilitated by authors RH and NR. Participation in the B-Well events is voluntary and not specific to ICU clinicians.

### Eligibility criteria {10}

Participants will be enrolled biweekly and are eligible if they are physicians (residents, fellows, and attendings), nurses, pharmacists, or therapists (respiratory, physical, speech) who have worked the equivalent of at least 1 full time work week (for their respective profession) in the ICU over the prior 4 weeks.

### Who will take informed consent? {26a}

Study investigators will obtain informed consent from potential trial participants. This will be done in person for participants recruited in person and electronically for participants recruited via e-mail. Study investigators will provide potential participants with information about the study, including the procedures involved for both arms of the study, risks of participation, and potential benefits of participation. Written informed consent will be obtained for subjects recruited in person. For subjects recruited via e-mail, online submission of the consent form will constitute informed consent.

### Additional consent provisions for collection and use of participant data and biological specimens {26b}

This trial does not involve collecting biological specimens for storage.

## Assignment of interventions: allocation

### Sequence generation {16a}

Randomization will utilize an online random number generator and will be performed in pairs such that each time a physician is randomized to a study arm, a non-physician will also be randomized to that study arm for balance.

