### Sample size {14}

The target enrollment is 200 ICU employees, of which we expect approximately 100 physicians and 100 non-physicians (nurses and therapists) in the study. This is based on a power analysis we performed for the ability to detect 20% reduction in burnout prevalence or a change of greater than 4 in mean Maslach Burnout Inventory Score (power of 0.8, alpha of 0.05).

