## Statistical methods

### Statistical methods for primary and secondary outcomes {20a}

Descriptive statistics will be reported for participant recruitment, study dropout, and engagement with the intervention. Baseline characteristics for each group will be reported. All analyses will be conducted on an intention-to-treat basis.

Unadjusted associations between independent risk factors (i.e., age, gender, and presence of primary or secondary outcome) will be assessed using Student’s *t* test or Wilcoxon rank sum test for continuous variables and a chi-square test for categorical variables. These risk factors and scores will be compared between the intervention and control group as well as analyzed from the beginning to the end of the intervention period (pre-survey compared to 3-month and 6-month scores). Mixed model regression will also be utilized to analyze differences between groups. Qualitative thematic analysis of free text response feedback regarding the intervention will be performed. All analyses will be performed using SAS Enterprise Guide 5.1 (SAS Institute, Inc., Cary, NC).

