### Challenges

While we aim to recruit a sample which represents all ICU employees, participants with burnout, depression, and anxiety symptoms may be difficult to engage in a research study. Feeling already overwhelmed, the employees most at risk may not engage with a time-consuming intervention, which could lead to underestimation of the intervention’s effect. We will do our best to increase subject participation by making participation in the study as convenient as possible using virtual platforms and by providing monetary reimbursement for the time participants spend completing surveys and participating in Death Café sessions.

We recognize that our intervention may have differential impact based on a number of factors. It is possible that burnout may vary at different times of the year with busier times leading to higher rates of burnout. The COVID-19 pandemic may increase the level of burnout and also limit the availability of those most in need to seek help. Certain demographic factors (marital status, having children, etc.), factors related to personal wellness (sleep, history of depression or anxiety, etc.), and those related to work environment (recent conflicts or deaths, etc.) may also play a role. We will not specifically recruit participants based on these factors, as our randomized controlled trial structure will help to account for these and other potential confounders. We will be performing multivariate regression analyses and other subgroup analyses to help us to evaluate these relationships. We hope to identify the employee subpopulations who benefit the most from Death Café debriefing sessions.

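### Physicians and non-physicians are allocated in same-arm pairs, but the stated between-arm tests use neither role nor pair; the net error is small and its direction unknown

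*Protocol article*

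**What the plan says.** **Allocation.** Sequence generation {16a} uses an online random number generator and works in pairs: "each time a physician is randomized to a study arm, a non-physician will also be randomized to that study arm for balance". Balance is the only reason given. Neither that section nor Concealment mechanism {16b} says how a physician and a non-physician come to be paired, and no shared ward, shift, team or site is mentioned.

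**Size.** Sample size {14} states "The target enrollment is 200 ICU employees, of which we expect approximately 100 physicians and 100 non-physicians (nurses and therapists) in the study". It aims for "the ability to detect 20% reduction in burnout prevalence or a change of greater than 4 in mean Maslach Burnout Inventory Score", with 80% power at a 5% significance level. No allowance for pairing appears.

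**Analysis.** Statistical methods {20a} lists Student's t, Wilcoxon rank sum and chi-square tests as unadjusted analyses. It then says that scores, as well as risk factors, are compared between the arms. It adds: "Mixed model regression will also be utilized to analyze differences between groups". The terms of that model are not given. Methods for additional analyses {20b} plans mixed-model subgroup analyses by role, and the Challenges section mentions multivariate regression. Pair is not named in any analysis.

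**The concern.** An analysis should reflect how people were allocated, and two features of this scheme matter.

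- **Role is balanced by construction.** Each arm receives one physician for every non-physician, so a burnout difference between roles cannot contribute to the difference between arms. A test that leaves role out still counts that difference as noise, and its standard error is too large.
- **Two people share one random draw.** If pair members have correlated outcomes, a test that counts 200 independent people has too small a standard error. One conceivable source is calendar time. Enrolment is biweekly, and the Challenges section says: "It is possible that burnout may vary at different times of the year with busier times leading to higher rates of burnout".

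The two errors run in opposite directions. At stake are the accuracy of the p-values and confidence intervals for the between-arm comparison, and some precision that the design has already paid for.

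**Working it through.** **Inputs from the documents:** 200 people, about 100 of each role, hence about 100 pairs and 50 pairs per arm at 1:1; power 0.80; alpha 0.05.

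**Assumptions, because the documents give no figure:** two-sided testing; control burnout of 60%, borrowed from Background and rationale {6a} ("The prevalence of burnout is as high as 60% in hospital employees at one of our institutions"); the 20% reduction read as 20 percentage points; role difference d of 0 to 0.8 within-role SDs; intraclass correlation r within pairs, given role, of 0 to 0.10.

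**1. The plan's own figure.** For 60% against 40%, with pooled variance and no continuity correction:

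n per arm = [1.96 × √(2 × 0.5 × 0.5) + 0.8416 × √(0.6 × 0.4 + 0.4 × 0.6)]² / 0.20² = (1.386 + 0.583)² / 0.04 ≈ 96.9, so 97 per arm and 194 in all.

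This is within 3% of 200, and power at 100 per arm is 0.812. So 200 reproduces as a count of independent individuals. The reproduction depends on the assumed control rate and on the absolute reading.

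**2. Standard errors under the actual scheme.** Take the within-role variance as 1.

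- A pair mean has variance (1 + r)/2. With 50 pairs per arm, the true variance of the difference is 2(1 + r)/100.
- A two-sample test on individuals sees variance 1 + d²/4 per person and uses 2(1 + d²/4)/100.
- Naive SE / true SE = √[(1 + d²/4)/(1 + r)].
- Type I error of the naive test = 2 × [1 − Φ(1.96 × ratio)].

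| d | r | naive SE / true SE | type I, formula | type I, simulated naive t test |
|---|---|---|---|---|
| 0 | 0 | 1.000 | 0.050 | 0.050 |
| 0.5 | 0 | 1.031 | 0.043 | 0.044 |
| 0.8 | 0 | 1.077 | 0.035 | 0.035 |
| 0 | 0.05 | 0.976 | 0.056 | 0.054 |
| 0 | 0.10 | 0.953 | 0.062 | 0.066 |
| 0.5 | 0.05 | 1.006 | 0.049 | 0.046 |
| 0.5 | 0.10 | 0.983 | 0.054 | 0.056 |

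The simulations used 100 pairs and 10,000 runs, so the simulation error near 0.05 is √(0.05 × 0.95/10,000) ≈ 0.002.

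**3. What each adjustment does (simulated).**

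- Role adjustment alone restores the level when r = 0: 0.051 at both d = 0.5 and d = 0.8.
- Role adjustment alone does not protect against similarity within pairs: 0.065 at d = 0.5, r = 0.10.
- A pair-level comparison stays between 0.048 and 0.055 in every scenario run.

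**4. Sample size.** With role ignored (d = 0), the design effect is 1 + r. From 194, the requirement is 198 at r = 0.02, 204 at 0.05 and 214 at 0.10. Power at 200 is 0.793 at r = 0.05 and 0.774 at 0.10. With d = 0.5 and r = 0.05, the true variance relative to the naive one is 1.05/1.0625 = 0.988, so the requirement would be slightly under 194.

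**The case against.** The strongest reply is that a condensed article need not list the terms of a mixed model. Role and pair may be in an analysis plan that is not shown, and role is already used in the subgroup analyses. This stands to an extent: a reader might infer that the trial ignores role, and the documents do not support that. It does not dispose of the point, because the allocation scheme and the two-sample tests are both stated. Those tests cannot carry either term, and the article presents the mixed model as an addition to them.

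Second, the within-pair correlation is conjecture. This also stands. No intraclass correlation is given, and pairing for balance gives no reason to expect a large one. A reader might infer that pair members join in the same biweekly cycle, but no section says that pairs are formed within a cycle. Seasonal variation in burnout is described only as possible. If r is zero, only the role effect remains, and it makes the tests conservative. It cannot inflate false positives.

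Third, adding role and a random pair effect to a logistic model would turn the binary burnout comparison into a conditional odds ratio. That is correct, and the fix has to allow for it.

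A reader might also infer that pairing without blocking breaks the statement "STOPTHEBURN is a parallel group randomized controlled trial with a 1:1 allocation ratio". It does not: equal-probability draws are compatible with a 1:1 ratio. Even a 40:60 split of pairs would keep 4 × 0.4 × 0.6 = 96% of the efficiency.

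**Conclusion.** The point holds as a modest mismatch between a stated allocation scheme and stated tests. Over the assumed ranges (d up to 0.8 SD, r up to 0.10), the naive standard error lies between about 5% too small and 8% too large, and type I error between about 0.035 and 0.062. The two effects nearly cancel at d = 0.5 and r = 0.05. The role part needs only a burnout difference between physicians and non-physicians. The pair part needs a correlation that the documents neither give nor imply.

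One tempting stronger reading is that only 100 units are randomised, so the trial is half its apparent size and underpowered. That would require pair members to be near copies of each other. At r = 0.10 the effective number is 200/1.10 ≈ 182, and power falls by about 4 percentage points. The target of 200 is therefore not shown to be wrong on this ground. Nor can one say that the standard errors of the mixed model are wrong, because its terms are not stated.

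**What to change.** - Record a pair number at randomisation and keep it in the analysis dataset. Anyone left without a partner forms a unit of one.
- Make the mixed model already planned in Statistical methods {20a} the main between-arm comparison. Include role (physician or non-physician) as a fixed effect. Handle pair by a random effect or pair-robust standard errors, in addition to the terms for repeated surveys on the same person.
- Keep the t, Wilcoxon and chi-square tests as descriptive, unadjusted results.
- For binary burnout, report a marginal estimate so that the estimand does not change, for example a risk difference standardised over role from GEE clustered on pair.

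The cost is one variable known at randomisation and a few sentences of text. In a simple comparison of the arms, error degrees of freedom would fall from about 198 (200 − 2) to about 98 (100 − 2), which barely moves the critical value. Recruitment, participants and the sample size are unaffected.
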